##### Other sleep outcomes

SE, SOL, WASO and TST will also be assessed with actigraphy to measure sleep objectively for 7 continuous nights. Actigraph is an objective measurement to assess sleep/wake behaviour for several continuous nights and days [81, 82]. It allows the participant to be mobile and to continue their normal routines while data are recorded in a natural sleep environment. In Sleep-RA, the actigraph is worn on the non-dominant wrist for 7 continuous nights and days. To validate or adjust the data from the actigraph, the participants write down their bed times and rise times and the use of the actigraph.

SE, SOL WASO and TST will be further assessed subjectively with the PSQI [72, 73].

##### Other RA outcomes

Fatigue severity, coping and effect over the previous 7 days will be assessed with the Bristol Rheumatoid Arthritis Fatigue Numerical Rating Scale (BRAF-NRS) on a scale of 0–10, with higher scores indicating greater severity. BRAF-NRS has shown good criterion and construct validity [83].

RA-related pain will be assessed with a self-reported visual analogue scale (VAS) for pain on a scale of 0–100, with a higher score indicating greater severity [84].

Functional status will be assessed with the Multidimensional Health Assessment Questionnaire (MD-HAQ) [85]. The MD-HAQ measures self-reported functional status over the previous 7 days on 10 items covering dressing, rising, eating, walking, hygiene, reach, grip and everyday activities. The mean of the MD-HAQ score is calculated with a possible range of 0.0–3.0, with a higher score indicating lower functional status. The MD-HAQ is validated for patients with RA and has a Cronbach’s α value of 0.65 for the psychological dimension and 0.88 for the physical dimension [86].

HRQoL will be assessed with the Short Form-36 health survey (SF-36) [87, 88]. This is a generic instrument consisting of 36 multiple-choice questions contributing to the sum scores of physical and mental health. The two scores of 0–100 are the weighted sums of the items in their section, with a higher score indicating less disability. The SF-36 is validated and translated to Danish. The Cronbach’s α value for SF-36 is >0.85 [89].

Disease activity will be assessed with DAS28-CRP. DAS28-CRP is a composite index developed to make an objective and reproducible assessment of RA disease activity and has been validated for use in clinical trials [90, 91]. A DAS28-CRP <2.6 implies remission, ≥2.6 and ≤3.2 implies low disease activity, >3.2 and ≤5.1 implies moderate disease activity, and >5.1 implies high disease activity.

Tender and swollen joints will be assessed by a physical examination of 28 joints, conducted by project nurses [92].

CRP will be assessed from serum samples. A higher CRP value indicates more inflammation [91, 93].

The patient global assessment of disease activity is a self-reported assessment of the patient’s overall assessment of how the arthritis is doing with the question: “Considering all the ways your arthritis affects you, rate how well you are doing on the following scale?” [94]. The patient reports “VAS global patient” from 0 to 100, with a higher score indicating more disease activity [95].

The physician global assessment is a well-validated assessment of the patient’s current disease activity [94]. The project nurses will report “VAS global physician” from 0 to 100, with a higher score indicating more disease activity [95].

#### Additional information

Additional information includes sociodemographic characteristics (education, employment, civil status, children living at home), lifestyle (smoking, alcohol, drugs, caffeine, physical activity), RA-related information (duration of RA, rheumatoid factor of the immunoglobulin M class, anti-citrullinated protein antibody, CRP), sleep-related information (duration of insomnia, sleep stages, number of awakenings, apnoea-hypopnoea index, leg movements), comorbidity (diabetes, hypertension, heart attack, other heart disease, stroke, chronic obstructive pulmonary disease, cancer, osteoarthritis, osteoporosis, asthma, depression) and current medicine (antirheumatic drugs, glucocorticoids, antidepressant drugs, hypnotic drugs).

### Participant timeline {13}

The trial period for each participant is approximately 6 months, and includes 6 weeks of CBT-i for participants in the intervention group and 20 weeks of subsequent outcome assessments for both groups. All participants will complete the same outcome assessments at baseline, after treatment (week 7) and at follow-up (week 26), as presented in Fig. 1 and Table 2.

**Table 2 Tab2:**
[figure not shown]
Standard Protocol Items: Recommendations for Interventional Trials (SPIRIT) trial schedule

*Primary outcome; ^†^key secondary outcomes; ^Δ^other secondary outcomes

*BRAF-MDQ* Bristol Rheumatoid Arthritis Fatigue Multidimensional Questionnaire, *BRAF-NRS* Bristol Rheumatoid Arthritis Fatigue Numerical Rating Scale, *CBT-i* cognitive behavioural therapy for insomnia, *CRP* C-reactive protein, *DAS28* Disease Activity Score-28, *HADS-D* Hospital Anxiety and Depression Scale-Depression, *HRQoL* health-related quality of life, *ISI* Insomnia Severity Index, *MDHAQ* Multidimensional Health Assessment Questionnaire, *PSG* polysomnography, *PSQI* Pittsburgh Sleep Quality Index, *RA* rheumatoid arthritis, *RAID* Rheumatoid Arthritis Impact of Disease, *SE* sleep efficiency, *SF-36* Short Form-36 health survey, *SOL* sleep-onset latency, *TST* total sleep time, *VAS* visual analogue scale, *WASO* wake after sleep onset

### Sample size {14}

With a total sample size of 60 patients with RA (30 allocated to CBT-i as treatment and 30 allocated to usual care), we will have more than 85% power to detect a group difference in the primary outcome of average SE assessed by PSG after treatment at week 7 and subsequently with reasonable power in the key secondary outcome assessed at follow-up at week 26.

For a two-sample pooled *t* test of a normal mean difference with a two-sided significance level of 0.05 (*P* < 0.05), assuming a common standard deviation of 7.5% in SE, a total sample size of 60 with allocation ratio of 1:1 has a power of 86.1% to detect a mean difference of 6 percentage points in SE.

The Sleep-RA trial is sufficiently powered to detect the anticipated difference with a total sample size of 52 participants. Assuming a balanced attrition rate (no more than four withdrawals per group) we will obtain enough statistical power (80.7%, i.e. >80%) to detect a mean difference of 6 percentage points in SE.

With a total sample size of 60 patients and assuming a balanced design (1:1), exploratory analyses of any of the secondary outcomes collected at week 26 will have enough statistical power (>80%) to detect a standardised mean difference of 0.80 (i.e. a Cohen’s effect size corresponding to a large clinical effect).

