### Statistical methods

#### Statistical methods for primary and secondary outcomes {20a}

All main analyses will be conducted based on the intention-to-treat (ITT) population. We plan to conduct both an analysis of the full analysis set (patients with outcome data available at baseline) and a per-protocol analysis so that any differences between them can be explicitly discussed and interpreted. The ITT principle states the effect of a treatment policy (i.e. the planned treatment regimen) rather than the actual treatment given. The consequence of conducting ITT analyses is that participants allocated to a treatment group should be followed up, assessed and analysed as members of that group, irrespective of their compliance to the planned course of treatment. Robustness is a concept that refers to the sensitivity of the overall conclusions to various limitations of the data, assumptions and analytic approaches to data analysis. Robustness implies that the treatment effect and primary conclusions of the trial are not substantially affected when analyses are carried out based on alternative assumptions or analytical approaches.

We will control the α level across only the most important hypotheses by use of a hierarchical testing strategy to preserve a type 1 error rate of 5% for the primary outcome of change in SE assessed after treatment at week 7, followed by SE assessed at follow-up after 26 weeks. All the patient-reported outcome measures and other secondary outcome measures will, by principle, only be clinically relevant after 26 weeks. The sleep-related key secondary outcomes (SOL, WASO, TST, insomnia and sleep quality) will only be considered statistically significant with a *P* value <0.01 (0.05/5). The RA-related key secondary outcomes (fatigue, impact of RA and depressive symptoms) will only be considered statistically significant with a *P* value <0.017 (0.05/3) as described in Fig. 2.

In the Sleep-RA trial with repeated measures, participants will be randomly assigned to treatment groups, and outcome observations are made at two time points on each patient. We anticipate that measures on the same patient at different times are correlated and that measures taken close together in time will be more highly correlated than measures taken further apart in time; observations on different patients will be assumed to be independent.

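### The stated power above 80% at a standardised difference of 0.80 does not hold for the eight key secondary outcomes at their own thresholds (P<0.01 and P<0.017)

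*Protocol article*

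**What the plan says.** The section 'Sample size {14}' sets its power for the primary outcome by a pooled two-sample t "test of a normal mean difference with a two-sided significance level of 0.05", a standard deviation of 7.5% and a difference of 6 percentage points in sleep efficiency. It gives 86.1% power with 60 patients and 80.7% with 52, after up to four withdrawals per group.

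Its opening paragraph promises reasonable power, without a figure, for the key secondary outcome at week 26. Its last paragraph does give a figure, for exploratory analyses with 60 patients in a 1:1 design: "any of the secondary outcomes collected at week 26 will have enough statistical power (>80%) to detect a standardised mean difference of 0.80". No significance level is attached to that sentence.

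The section 'Statistical methods for primary and secondary outcomes {20a}' then sets the decision rule: "The sleep-related key secondary outcomes (SOL, WASO, TST, insomnia and sleep quality) will only be considered statistically significant" if P is below 0.01 (0.05/5). Fatigue, impact of RA and depressive symptoms need P below 0.017 (0.05/3). The objectives and the key secondary outcomes section place all eight outcomes at week 26.

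**The concern.** The power statement and the decision rule use different significance levels. A standardised difference of 0.80 is the primary assumption again (6/7.5), so the figure above 80% looks like the primary calculation at 0.05 carried over to week 26. The words 'any of the secondary outcomes' take in the eight key secondary outcomes, whose thresholds are three to five times stricter.

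These outcomes carry the week-26 conclusions on insomnia, sleep quality, fatigue, impact of RA and depressive symptoms. A reader who relies on the sample size section would take a non-significant result on one of them as coming from a test with more than 80% power for a large effect. At the thresholds actually used, the protocol's own calculation does not support that.

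**Working it through.** **Inputs**

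- Arm size n: 30 with all 60 patients, 26 with 52 ('Sample size {14}').
- Standardised difference d: 0.80, as stated for week 26; equal to 6/7.5 for the primary outcome.
- Test: two-sided pooled two-sample t test ('Sample size {14}').
- Thresholds: 0.05 ('Sample size {14}'); 0.05/5 = 0.01 and 0.05/3 = 0.0167, printed as 0.017 ('Statistical methods {20a}').

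**Formula**

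Degrees of freedom are 2n − 2 and the noncentrality is d × √(n/2). Power is the probability that a noncentral t variable exceeds the two-sided critical value; the opposite tail is negligible.

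- n = 30: df = 58, noncentrality = 0.80 × √15 = 3.098.
- n = 26: df = 50, noncentrality = 0.80 × √13 = 2.884.

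**Step 1: reproduce the protocol's figures at 0.05**

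- n = 30, critical value 2.002: power 86.1%, as stated.
- n = 26, critical value 2.009: power 80.7% (0.8075), as stated.

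The method is therefore the protocol's own, and the claim above 80% is true at 0.05.

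**Step 2: same calculation at the key secondary thresholds**

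| Threshold | Outcomes | Critical value, n = 30 | Power, 60 patients | Critical value, n = 26 | Power, 52 patients |
|---|---|---|---|---|---|
| 0.01 | five sleep | 2.663 | 66.8% | 2.678 | 58.4% |
| 0.05/3 | three RA | 2.465 | 73.5% | 2.477 | 65.8% |

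Using 0.017 as printed instead of 0.05/3 changes the last row only slightly, to 73.7% and 66.1%.

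**Step 3: difference detectable with 80% power**

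Solving the same formula for d:

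| Threshold | 60 patients | 52 patients |
|---|---|---|
| 0.05 | 0.74 | 0.79 |
| 0.05/3 | 0.86 | 0.92 |
| 0.01 | 0.91 | 0.98 |

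**Step 4: what the baseline covariate could add**

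The planned mixed model includes the baseline level. If r is the correlation between baseline and week 26, the effective standardised difference is about 0.80/√(1 − r²). The protocol gives no r, so the values below are assumptions.

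| Assumed r | Effective d | 60 patients: 0.01 / 0.05/3 | 52 patients: 0.01 / 0.05/3 |
|---|---|---|---|
| 0.3 | 0.839 | 72% / 78% | 64% / 71% |
| 0.5 | 0.924 | 82% / 86% | 74% / 80% |
| 0.7 | 1.120 | 95% / 97% | 91% / 94% |

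With 60 patients, 80% is passed from about r = 0.5 at 0.01 and from about r = 0.4 at 0.05/3.

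**The case against.** **The sentence speaks of exploratory analyses.** The opening paragraph of the section treats the key secondary outcome separately and promises only reasonable power. One could read the two together as above 80% for unadjusted comparisons and an unquantified promise for the key secondary outcomes. This is a fair reading of intent, but the sentence says 'any' secondary outcome at week 26 and states no level, so the key secondary outcomes fall within it. On either reading the wording needs correcting.

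**The arithmetic is right.** Every power figure in the section reproduces at 0.05. That stands: the fault is that the figure is applied to tests made at other levels.

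**The analysis adjusts for baseline.** This also stands as a limit. A reader might infer that a true standardised difference of 0.80 would be missed about one time in three for sleep outcomes and one in four for RA outcomes. The documents do not support that as the real rate: 66.8% and 73.5% are for an unadjusted t test, and the planned model could do better. Nor do they support the opposite inference that adjustment restores 80%, since no correlation is assumed anywhere.

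**Not all secondary outcomes are affected.** A reader might infer that every week-26 secondary outcome falls short. Only eight have reduced thresholds. Week-26 sleep efficiency and the other secondary outcomes, such as pain, functional status, quality of life, disease activity and actigraphy, have none.

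**Conclusion.** The power statement is wrong as written for the eight key secondary outcomes. With 60 patients and a standardised difference of 0.80, power on the protocol's own basis is 66.8% at 0.01 and about 73.5% at 0.05/3, against a stated figure above 80%. The shortfall is present at full enrolment; it grows to 58.4% and 65.8% at the attrition the protocol allows for.

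This rests on the protocol's two-sided pooled t test, equal arms and no gain from the baseline covariate. For week-26 sleep efficiency and the other secondary outcomes, the statement stands at two-sided 0.05 with 60 patients. The primary outcome's power is correct, and nothing here suggests that the trial is too small for its primary question or that its multiplicity rule is invalid.

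**What to change.** In 'Sample size {14}', limit the statement of more than 80% power to comparisons at two-sided 0.05, and add a sentence for the key secondary outcomes. For example:

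*At the multiplicity-adjusted levels, 60 (52) patients give 67% (58%) power at P<0.01 for each sleep-related key secondary outcome, and 73% (66%) at P<0.017, calculated as 0.05/3, for each RA-related one, at a standardised difference of 0.80. Power of 80% requires 0.91 (0.98) and 0.86 (0.92). These figures are for an unadjusted t test; the planned adjustment for baseline may raise them.*

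If the investigators want to quantify that gain, they should state the assumed correlation. For 0.3 to 0.7, power with 60 patients would be about 72–95% at 0.01 and 78–97% at 0.05/3.

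The cost is a less favourable stated power. The sample size, the thresholds, the analysis and the conduct of the trial stay as they are.

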### Recruitment {15}

All patients at routine rheumatologic outpatient visits in Denmark enter self-reported data on a touch screen linked to the National Clinical Database for Rheumatology (DANBIO) [96]. Potential participants for Sleep-RA will be identified when they answer the question: “At this moment, are you able to get a good night’s sleep?” Patients who answer either “With much difficulty” or “Unable to” will be presented with a pop-up message on the screen containing brief information that a research project on sleep is underway (and currently recruiting participants). Patients who want further information can type “yes” on the screen. [name] will telephone each patient and will offer to send written information and subsequent oral information. While giving the oral information, it will be determined whether the patient fulfils the criteria and can enter the trial.

Patients who are not eligible or do not wish to participate in the trial will be registered in one of the following three categories: 1) did not meet the inclusion criteria; 2) declined to participate; or 3) other reasons (Fig. 1).

### Assignment of interventions: allocation

#### Sequence generation {16a}

Randomisation will be conducted after baseline assessment by computer-generated random numbers with blocks of ten participants.

During randomisation, participants will be stratified by disease activity to equalize the risk of change in treatment with antirheumatic drugs during the trial period and the effect this might have on sleep. Stratification will be set to disease activity according to DAS28-CRP ≤3.2 (low disease activity) and >3.2 (moderate disease activity) measured at baseline [97].

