### Trial design {8}

The Sleep-RA trial will be carried out as a randomised controlled trial with a two-group parallel design. Participants (*n* = 60) will be allocated 1:1 to either CBT-i as treatment (intervention group) or to usual care (control group). Outcome assessments will be conducted three times for each participant: at baseline, after treatment (week 7) and at follow-up (week 26), as presented in Fig. 1.

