### Who will take informed consent? {26a}

The corresponding author ([name]) is the project manager of Sleep-RA and will obtain informed consent from participants.

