#### Concealment mechanism {16b}

Allocation concealment will be ensured as it will not be possible to conduct the computer-generated randomisation until the baseline assessment is completed for each participant.

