#### Implementation {16c}

An external collaborator (Zitelab Aps, http://www.zitelab.dk/) will generate the allocation sequence. This collaborator is not involved in outcome assessments or the CBT-i intervention. [name] will enrol participants and, immediately after randomisation, inform them to which group they have been allocated.

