#### Procedure for unblinding if needed {17b}

The trial design is open-label with only the outcome assessors being blinded so unblinding will not occur.

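### A single stated block size of ten, in an open-label trial whose enroller learns every allocation, leaves some assignments inferable, so the protocol's concealment claim is too strong

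*Protocol article*

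**What the plan says.** Sequence generation {16a} gives one block size: "Randomisation will be conducted after baseline assessment by computer-generated random numbers with blocks of ten participants". The same section adds two strata: "Stratification will be set to disease activity according to DAS28-CRP ≤3.2 (low disease activity) and >3.2 (moderate disease activity) measured at baseline". Trial design {8} sets a 1:1 ratio for 60 participants, so each block holds five places per arm.

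Concealment mechanism {16b} reads: "Allocation concealment will be ensured as it will not be possible to conduct the computer-generated randomisation until the baseline assessment is completed". It gives no other reason. Implementation {16c} adds that an external company with no part in outcome assessment or therapy generates the sequence. It also says that a member of the trial team "will enrol participants and, immediately after randomisation, inform them to which group they have been allocated". On blinding, section {17b} states: "The trial design is open-label with only the outcome assessors being blinded so unblinding will not occur".

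Recruitment {15} places the eligibility decision in personal contact before randomisation: "While giving the oral information, it will be determined whether the patient fulfils the criteria and can enter the trial". Section {26a} says that the corresponding author "is the project manager of Sleep-RA and will obtain informed consent from participants".

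**The concern.** Concealment can fail in two ways: someone reads the next code, or someone works it out. The external sequence and the rule that randomisation follows baseline deal with the first. Neither deals with the second. If the block size is constant and known, and every past allocation is visible, a person can count the arms within a stratum. Once five places of one arm have been used, the rest of that block is known. Nothing in the article withholds the block size from the person who enrols.

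There is room to act on such knowledge. Some eligibility criteria need judgement, such as whether a change in antirheumatic treatment is indicated, or whether personal circumstances impede adherence. Assessment dates are planned individually (section {18b}), which affects who enters a block when. Selection of this kind happens before randomisation, so intention-to-treat analysis does not remove it. With 30 per arm, steering a few patients could shift prognosis between the arms.

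**Working it through.** The protocol gives no figure for predictability. Its power figures reproduce with the noncentral t (86.14% for the stated 86.1% at 30 per arm, 80.75% for the stated 80.7% at 26 per arm) and do not depend on this point.

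**Inputs.** Block of ten, 5:5 (sections {16a} and {8}); 60 participants; two strata. Stratum sizes are not given, so 30/30, 25/35 and 18/42 are assumed. The guesser is assumed to know the block size, all earlier allocations in the stratum and the patient's stratum.

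**1. Determined places per block.** Let L be the number of places at the end of a block that all belong to one arm. Then P(L ≥ k) = 2·C(10−k, 5)/C(10, 5):

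- k = 1: 252/252 = 1
- k = 2: 112/252 = 0.444
- k = 3: 42/252 = 0.167
- k = 4: 12/252 = 0.048
- k = 5: 2/252 = 0.008

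The sum is E[L] = 1.67, which agrees with 2b/(b+1) = 10/6 for b = 5.

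**2. Over 60 participants.**

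- Six complete blocks (30/30): 6 × 1.667 = 10.
- Strata of 25/35: five complete blocks and two part-blocks of five places. No place among the first five can be determined, so 5 × 1.667 = 8.33 (simulation 8.36).
- Strata of 18/42: five complete blocks, a part-block of eight places and one of two. The eight-place part adds 0.008 + 0.048 + 0.167 = 0.22, giving 8.33 + 0.22 = 8.55 (simulation 8.52).

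About 8 to 10 of 60 are therefore certain, or one in six or seven.

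**3. Best guess overall.** Always guessing the arm with more places left is right for 5 + (2^10/252 − 1)/2 = 5 + (4.063 − 1)/2 = 6.53 of every 10, or 65.3%, against 50% by chance.

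**4. Patients awaiting randomisation.** If one patient in the same stratum is already ahead in the queue, the determined places per block fall to 1.67 − 1 = 0.67, or 6 × 0.67 = 4 of 60. With two ahead, they fall to 0.67 − 0.44 = 0.22, about 1.3 of 60. How many are usually pending is not stated.

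**5. Effect of varying the size.** Simulation with 1,500 runs per stratum; the guesser knows the set of sizes but not the current one. Ranges cover the three assumed stratum splits.

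| Block sizes | Certain, of 60 | Best guess right |
|---|---|---|
| 10 only | 8.4–10.0 | 63.8–65.3% |
| 4, 6, 8 | 1.4–1.5 | 67.2–67.5% |
| 6, 8, 10 | 1.0–1.1 | 65.4–65.6% |
| 8, 10, 12 | 1.0 | 64.0–64.4% |

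Varying the size removes most of the certainty but hardly moves the overall guess rate, and the small set raises it.

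**The case against.** The strongest reply is that exploiting a prediction is harder than the counting suggests. Eligibility is judged during the oral information, while allocation is drawn only after a baseline that includes home polysomnography and seven nights of actigraphy. The enroller would have to anticipate the stratum, which rests on a nurse's joint count and a laboratory CRP, and also who else in that stratum is randomised first. Therapy in groups of two to six makes clustered enrolment plausible. This stands in part: it lowers the number of usable certain allocations, as step 4 shows. It does not bring it to zero, and an approximate DAS28-CRP is probably known early because a value of at most 5.1 is an inclusion criterion.

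Ten is also among the less predictable choices. Known blocks of four would leave 33% of allocations determined and 71% guessed correctly. The external generator is a real safeguard. The primary outcome is polysomnographic sleep efficiency, handled by blinded assistants, and the model adjusts for baseline level and stratum. All of this limits the harm. Blinded assessment does not act on selection before randomisation, however, and adjustment does not reach unmeasured prognosis.

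A reader might infer that self-report bias in the five patient-reported key secondary outcomes is part of this problem. It is not: it would arise under any block scheme in an open-label trial.

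**Conclusion.** The point holds as a modest design weakness. The stated reason for concealment does not deliver what is claimed, because timing blocks access to the next code but not inference from past ones. About 8 to 10 of 60 allocations are certain for an informed guesser, and fewer when patients in the same stratum are pending. Power and sample size are unaffected.

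This rests on three assumptions: that a single stated size means a constant one (the article does not use the word fixed), that the enroller knows that size, and that the stratum can be anticipated. Names are removed, so it cannot be confirmed that the enroller is the project manager who takes consent. The point does not need this, since whoever enrols learns the allocations and the block size is stated in the protocol.

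Two stronger readings are tempting. One is that allocation has been or will be steered, or that the primary result is biased; the document gives no evidence of that and no basis for a bias estimate. The other is that a 65% guess rate is a defect which varying block sizes would cure; the table shows it is not.

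**What to change.** For blocks not yet issued, ask the external collaborator to draw block sizes at random within each stratum and to withhold them from everyone who enrols. Sets such as 8, 10 and 12, or 6, 8 and 10, are preferable to 4, 6 and 8, which raise the guess rate to about 67%. Expect certain allocations to fall to about 1 of 60, with the best-guess rate staying near 64–66%.

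Reword Concealment mechanism {16b} so that concealment rests on the external sequence and on undisclosed, varying block sizes, with the timing of randomisation as a supporting measure. The sizes themselves should stay out of documents the trial team can see until recruitment ends. If no blocks remain, the rewording should drop the claim that concealment is ensured and describe the scheme actually used.

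The cost is a setting change at the provider and a short amendment. Arms fill slightly less evenly, which matters a little for forming therapy groups. Blocks already issued cannot change: recruitment began on 17 December 2018, this version is dated 16 January 2020, and the number of blocks left is not stated.
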